## Abstract

Moringa oleifera is an herbal galactagogue that has been used to increase the volume of breastmilk. Few studies have evaluated the effect of Moringa oleifera in breastfeeding. There are conflicting data whether it can increase the volume of breastmilk or not. Thus, the objective of this study is to evaluate the efficacy of Moringa oleifera leaves in increasing the volume of breastmilk in early postpartum mothers. A randomized, double-blind, placebo-controlled trial will be conducted. The outcomes of this study will provide the data of Moringa oleifera as an herbal medication to increase the volume of breastmilk. This information will be used to increase the rate of exclusive breastfeeding for the first 6 months as recommended by the World Health Organization.

Clinical trial registration

This clinical trial was registered at ClinicalTrials.gov (Clinical trials registration: NCT04487613).

## Introduction

Breastmilk is the best food for the baby. It is safe, clean and contains antibodies which protect them against common illnesses. It also contains good nutrients and energy for the baby, especially in the first month of life. Breastfeeding provides physiological and health benefits for both the mother and the baby. World Health Organization (WHO) and United Nations International Children’s Emergency Fund (UNICEF) recommend that the baby be breastfed within the first hour of life and exclusively for the first 6 months of life. WHO actively promotes breastfeeding as the best source of nourishment for infants and young children, and has set the rate of exclusive breastfeeding for the first 6 months up to at least 50% by year 2025 [1].

Adequate volume of breast milk is the factor for success in exclusive breastfeeding. Various methods have been used to increase the volume of breast milk. From the Cochrane database systemic review in 2020, demonstrated that natural milk boosters may improve milk volume and infants’ weight, but they are very uncertain about the supporting evidence. More high-quality studies are needed to increase the certainty about the effects of milk boosters [2]. Galactagogue herbs have been used by breastfeeding mothers who have breastmilk problem to increase the volume of breastmilk [3]. Moringa oleifera is an herbal galactagogue. Moringa oleifera is one of the herbs that has been used to increase the volume of breastmilk. Moringa oleifera are widely used in traditional medicine. Moringa oleifera leaves and immature seed pods are used as food products [4]. Moringa oleifera leaves increases breastmilk volume by increasing prolactin and providing essential nutrients [2, 5]. It takes about 24 hours after ingestion for the Moringa oleifera to work [6, 7]. Various safety studies were conducted in animals using aqueous leaf extracts and the results indicated that there was a high degree of safety. No adverse effects were reported in human studies [4]. There have been few studies that have evaluated Moringa oleifera in breastfeeding. One study found that the consumption of moringa cookies increased the quality of breastmilk, especially the amount of protein [8]. Another study found that Moringa oleifera leaves increased the production of breastmilk on postpartum days 4 to 5 among mothers who delivered preterm infants [7]. One study found that women who took Moringa oleifera capsules had more breastmilk per day from postpartum days 3 to 10 compared to those women who were on placebo. However, this was not statistically significant [6]. Thus, the objective of this study is to evaluate the efficacy of Moringa oleifera leaves in increasing the volume of breastmilk in early postpartum mothers.

## Materials and methods

This randomized, double-blinded, placebo-controlled trial will be performed at the Department of Obstetrics and Gynecology, King Chulalongkorn Memorial Hospital, Faculty of Medicine, Chulalongkorn University, Bangkok, Thailand. This is a baby friendly hospital. This study was approved by the Research Ethics Committee of the Faculty of Medicine, Chulalongkorn University (IRB No. 157/63). The study will be performed in accordance with the approved guidelines of the Research Ethics Committee. Written informed consent will be obtained from all participants. This clinical trial was registered at ClinicalTrials.gov (Clinical trials registration: NCT04487613). The authors confirm that all ongoing and related trials for this drug are registered. The complete date range for participant recruitment and follow-up will be 1 year and 6 months (November 1, 2020 –April 30, 2022).

Pregnant women aged 18 years or more and gestational age 37 weeks or more who intend to breastfeed will be invited to join this study. Recruitment is done and consent is obtained before delivery. Randomization will be done after delivery. Women with uncomplicated full term delivery who have accomplished similar antenatal breastfeeding promotion protocol will be included. Postpartum women with contraindication to breastfeeding such as HIV, on chemotherapeutic drugs, on radioactive substances, baby with galactosemia, postpartum women with unstable conditions (i.e., postpartum hemorrhage, sepsis), known allergy to Moringa oleifera, women whose baby need phototherapy, women with insufficient glandular tissue or breast surgery, women with a history of infertility, women with hypothyroidism, women with twins or higher order births, premature infants and infants with sucking problems or structural oral anomalies that can affect sucking (e.g. tongue tie, birth asphyxia, clefts, etc.) will be excluded.

After the study is approved, eligible consecutive postpartum women during the study period who gave informed consent will be enrolled into the study. All women will receive the same postpartum care along with breastfeeding support procedures. The research nurses confirm that all women correctly nursed their infants. Breastfeeding will be initiated immediately after delivery in all women. All women will be encouraged to breastfeed their baby as frequently as they desired or whenever the baby becomes hungry. The babies will be fed directly from the breasts. All women will be exclusively breastfeeding, and their baby will not be given any supplemental feeds. If the baby shows signs of inadequate milk intake, and if supplemental feeds are given, these are controlled for in the analysis. The data about supplemental feeds will be recorded from asking the women.

The drugs and placebo will be prepared prior to the study by a pharmacist who is not involved in the study. For the treatment capsule, it will contain 450 mg of Moringa oleifera leaves. As for the placebo capsule, there will be no content in the capsule. The participants will be asked if they think they got the placebo or the intervention to check on how effective the blinding was.

The participants will be randomized into two groups: treatment or placebo groups. A randomization scheme will be generated by a random number table using a block-of-four technique. The co-investigator, who has no contact with the participants, will generate the allocation sequence prior to the study. To ensure randomization, each envelope will be distributed in a sequential numerical order. Both the health care providers and the participants will be masked to the treatment assignment.

The nurses will enroll the participants. As soon as the participant meets the inclusion criteria, the nurses will proceed to select a sequentially numbered opaque envelope. The opaque envelopes will contain 6 capsules of Moringa oleifera leaves powder or placebo (identical in size, shape, and color). The opaque envelopes are sealed to ensure the allocation sequence is secure. The treatment group will receive Moringa oleifera leaves powder (450mg per capsule) (Ouay Un Osoth, Thailand) and the placebo group will receive no drug capsules. All women will take 1 capsule of the Moringa oleifera or placebo 2 times before meal for 3 days. Participants will take their first capsule at first 6 hours of birth. Treatment assignment will not be revealed until data collection is completed 6 months later. All women will be admitted into the postpartum ward and discharged on the fourth day postpartum. Hence, all women will receive all of their medications. The research nurses will capture the measures outcome and 8 personnel involve in this study. The dosage of 450 mg Moringa oleifera leaves powder is used in the study due to the recommendation from Thai traditional medicine for galactagogue. This dosage is higher than previous studies [6, 7].

The primary outcome is the volume of breastmilk on the third day postpartum. Secondary outcomes will assess the delta daily milk volume of consecutive 3 daily postpartum, time to noticeable breast fullness, the maternal satisfaction, quality of life, side effects, and the exclusive breastfeeding rates at 6 months (Fig 1). The third day is used as the measurement time point because it represents the timing of stage II lactogenesis [6]. The weighing method will be used on the third day postpartum (48–72 hour). The weighing procedure will start at 48 hours after delivery in all women. The nurse will weigh the infant fully clothed before and after each feeding using an electronic weight scale (Camry ER 7210, accurate to 5 g) for the period of 24 hours. The numbers of times weight measures taken will be 8–12 depending on frequency of breastfeeding of each participant. The baby would be weighed each time she/he wants to feed, even if it’s a baby who wants the breasts every 20 minutes.

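### The placebo capsule is specified as empty against an active capsule holding 450 mg of powder, so the claimed double-blind is not secured

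*Protocol article*

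**What the plan says.** All of the relevant text is in the protocol article, Materials and methods.

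- **Design label:** "This randomized, double-blinded, placebo-controlled trial will be performed".
- **Active product:** "For the treatment capsule, it will contain 450 mg of Moringa oleifera leaves".
- **Placebo:** "As for the placebo capsule, there will be no content in the capsule".
- **Matching:** "The opaque envelopes will contain 6 capsules of Moringa oleifera leaves powder or placebo (identical in size, shape, and color". Mass, fill, feel, taste and smell are not mentioned.
- **Masking claim:** "Both the health care providers and the participants will be masked to the treatment assignment".
- **Placebo arm, described again with the envelopes:** "the placebo group will receive no drug capsules".

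Each woman takes one capsule twice a day for three days. Nurses who enrol pick the next numbered, sealed envelope, and research nurses record the outcomes. Women will be asked which arm they believe they were in, as a check on blinding. No such question is described for the nurses.

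**The concern.** Matching on appearance is not enough when one capsule is full and the other is empty. The article states this composition outright, so it is not a detail left to a fuller document. Sealed opaque envelopes conceal the next assignment, but they do not mask a capsule once it is in the hand.

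Most secondary outcomes are what the woman reports: when her breasts felt full, satisfaction, quality of life, whether she thought the capsules helped, side effects, and breastfeeding at six months. A woman who suspects that her capsule is empty may answer differently. The primary outcome, milk volume on day 3, is weighed and so better protected. However, nurses do the weighing, and the total can depend on how often the mother feeds. If the trial is positive, a critic could put part of the result down to unblinding, and no analysis could fully answer that.

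**Working it through.** **1. The product as specified.**

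| Feature | Active | Placebo |
|---|---|---|
| Fill | 450 mg leaf powder | none |
| Size, shape, colour | matched | matched |
| Mass, feel, taste, smell | not stated | not stated |

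Capsules per woman: 2 per day × 3 days = 6, which agrees with six per envelope. Difference per capsule: 450 − 0 = 450 mg. Difference per envelope: 6 × 450 mg = 2.7 g.

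**2. Relative mass (assumption).** The article gives no shell weight. For an assumed shell of 60 to 150 mg, the ratio of filled to empty is (450 + 60)/60 = 8.5 down to (450 + 150)/150 = 4.0.

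**3. The plan's only related figure.** The control mean is 135.0 mL, the SD 61.5 mL and the expected gain 30%, so the target difference is 0.30 × 135.0 = 40.5 mL. With two-sided α = 0.05 and power 0.80, n = 2 × [61.5 × (1.960 + 0.842)/40.5]² = 36.2 per group. Then 36.2 × 1.2 = 43.4, rounded up to the stated 44. The blinding point does not change this number. It gives the placebo quantity: 44 × 6 = 264 capsules.

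**4. Why the primary outcome is less exposed but not immune.** The article expects 8 to 12 weight measures in 24 hours, on a scale accurate to 5 g. If these are feeds, the target difference per feed is 40.5/12 = 3.4 mL to 40.5/8 = 5.1 mL. If they are single weighings, two per feed, there are 4 to 6 feeds and the range is 40.5/6 = 6.8 mL to 40.5/4 = 10.1 mL. At 1 g = 1 mL, the effect per feed is of the same order as the scale's accuracy. A small, consistent lean in readings, or more frequent feeding in one arm, could therefore matter.

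**5. Illustration only.** Suppose there is no true effect and unblinding shifts the mean difference by an assumed b mL. The standard error is 61.5 × √(2/n), which is 14.7 mL for 35 per arm (44 × 0.8, rounded) and 13.1 mL for 44. The two-sided false-positive rate is 1 − Φ(1.96 − b/SE) + Φ(−1.96 − b/SE).

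| Assumed b | 35 per arm | 44 per arm |
|---|---|---|
| 5 mL | 6.3% | 6.7% |
| 10 mL | 10.4% | 11.9% |
| 15 mL | 17.5% | 20.8% |
| 20 mL | 27.5% | 33.2% |

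The document supports none of these values of b. The table shows only what a given bias would do to the nominal 5%.

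**The case against.** **In the plan's favour.** In a parallel design each woman sees one capsule type, so no participant can compare the two. The article says that nurses select a sealed envelope, not that they open it or handle capsules. The primary outcome is an electronic weight difference over a fixed 24-hour window. The guess question shows that the investigators thought about blinding. All of this stands, and it limits what can be claimed: the article cannot show how many women or nurses would notice. It does not repair the product, because a woman may still recognise an empty capsule without a full one beside it.

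**The later wording on the placebo arm.** The phrase "the placebo group will receive no drug capsules" could be read as capsules without drug, which would allow an inert filler. It could also be read as no capsules at all, but the article has all women taking capsules. Neither reading displaces the plain statement that the placebo capsule has no content.

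**Stronger readings that the document does not support.**
- A reader might infer that the fixed blocks ("A randomization scheme will be generated by a random number table using a block-of-four technique") make later assignments predictable once staff recognise the capsules. That needs staff who identify every earlier allocation and know both the block size and where each block starts, and the article says none of this. If staff could tell envelopes apart by weight, they would know the next assignment whatever the block size. If the capsules were matched, this route would close.
- A reader might infer that an empty shell can be squeezed flat or that the powder has a telling smell. Shell material and odour are not described, so these are assumptions.
- A reader might infer that nurses who know the arm would steer supplemental feeding. The article ties supplements to signs of inadequate intake and records them by asking the women. It does not say that nurses decide on them.

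**Conclusion.** The concern holds in this form: the placebo is specified without fill, the match covers appearance only, and so the masking that the article claims is not secured. The firm part is the difference of 450 mg per capsule and 2.7 g per envelope, which follows directly from the text. The exposure is mainly in the self-reported outcomes. For the weighed primary outcome it is smaller but not absent.

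The direction and size of any bias cannot be derived from the document, and the false-positive rates above depend entirely on assumed shifts. It would go too far to say that unblinding is certain or that the primary result would be invalid. The point still deserves correction before enrolment, because a blind lost during the trial cannot be restored in the analysis.

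**What to change.** **Before enrolment:** replace the sentence that leaves the placebo capsule without content. State that the pharmacist fills it with an inert powder to the same mass as the active capsule, in opaque shells, and add mass to the list of matched features. The cost is filler for about 264 capsules, made by the pharmacist who already prepares them, and an ethics notification of the placebo composition. The sample size does not change.

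**If capsules are already in use:** a switch midway would create two kinds of placebo. Instead, also ask the nurses who weigh the infants to guess the arm, report a pre-specified blinding index for women and nurses, and qualify the double-blind claim in the report. This costs one extra question and a short analysis. It documents the state of the blind but does not restore it.

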**Fig 1 pone.0248950.g001:**
[figure not shown]
Recommended content for the schedule of enrolment, interventions, and assessments. *Recommended content can be displayed using various schematic formats. See SPIRIT 2013 Explanation and Elaboration for examples from protocols. **List specific timepoints in this row. *t*_*1*_: postpartum day 1, *t*_*2*_: postpartum day 2, *t*_*3*_: postpartum day 3, *t*_*4*_: six months postpartum.

The volume of the breastmilk will be evaluated. The sum of the weight difference in gram will be converted into the volume of the breastmilk in milliliter (1 g = 1mL). This method is comparable with the measurement of the volume of the breastmilk based on deuterium oxide dilution technique from a previous study [9–11].

Time to noticeable breast fullness is defined as the mean time from birth to noticeable breast fullness. The participants will be asked if they noticed their breasts were full and followed by ‘When did you feel breast fullness?’.

Satisfaction and quality of life will be asked at postpartum day 7 via a phone interview. Satisfaction answer choices will consist of the following: very satisfied, satisfied, neutral, unsatisfied, and very unsatisfied. Quality of life will be assessed by WHOQoL-BREF [12]. The participants will be asked with “Did the capsules help?”. Side effects are recorded at postpartum day 3 by interview and at postpartum day 7 via a phone interview. The exclusive breastfeeding rates and any breastfeeding at 6 months will be asked via a phone interview.

The sample size calculation is based upon the findings from a previous study [13]. Two-tailed test is used. The average volume of breastmilk on 3 days postpartum was 135.0 ± 61.5 mL. We expect that there will be a 30% increase in the volume of the breastmilk. With adjustments for a withdrawal rate of 20%, a minimum of 44 women in each group are required to detect statistical difference (α = 0.05, β = 0.2) between the two groups. Therefore, a total of 88 women are required for this study.

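### A published fixed block size of four would let nurses deduce up to a third of allocations if opened capsules reveal the arm; varying the blocks is a cheap, minor improvement, secondary to the unmatched placebo

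*Protocol article*

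**What the plan says.** All of this stands in the protocol article under Materials and methods.

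- **Sequence.** "A randomization scheme will be generated by a random number table using a block-of-four technique". There are two arms ("The participants will be randomized into two groups: treatment or placebo groups"). The list is made before the study by a co-investigator who does not meet participants.
- **Size and ratio.** The sample-size paragraph says "a minimum of 44 women in each group are required to detect statistical difference" and "Therefore, a total of 88 women are required for this study". The ratio is therefore 1:1, and each block of four holds two active and two placebo sets.
- **One series.** The trial "will be performed at the Department of Obstetrics and Gynecology, King Chulalongkorn Memorial Hospital", and "each envelope will be distributed in a sequential numerical order". No stratification factor is named.
- **Handling.** Nurses enrol the women; once a woman qualifies, "the nurses will proceed to select a sequentially numbered opaque envelope". The envelopes are sealed and hold six capsules. Research nurses record the outcomes.
- **Capsules.** The active capsule holds 450 mg of leaf powder. "As for the placebo capsule, there will be no content in the capsule". The stated match covers size, shape and color; weight is not mentioned.
- **Safeguards.** Providers and participants are to be masked. Consent is taken before delivery, randomization follows delivery, and eligible women are enrolled consecutively. Participants will be asked which arm they think they had, as a check on blinding.

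**The concern.** Fixed blocks do no harm while past assignments stay unknown. If they become known, the block size turns them into knowledge of assignments still to come. Here the size is printed in the protocol. With one unstratified series the boundaries are plain: envelopes 1 to 4, 5 to 8, and so on. Sealing an envelope hides its own contents, but does not prevent deduction from those already opened.

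The capsules give a possible way to learn past assignments. Six active capsules carry 6 × 450 mg = 2.7 g of powder, and six placebo capsules carry none. The protocol does not say that anyone can tell them apart, but it claims no match on weight.

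A nurse who knows the next assignment could decide a borderline eligibility question accordingly, or change the order in which two women are randomized. Some exclusions can be judged only after delivery, such as an unstable maternal condition or an infant's sucking problem, so there is room for this. The groups could then differ at baseline in ways that affect the day-3 milk volume.

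**Working it through.** **Inputs from the protocol.** Two arms, 1:1, blocks of four, 88 women, hence 88 / 4 = 22 complete blocks. The total reproduces from the stated assumptions. With SD 61.5 mL and a difference of 0.30 × 135.0 = 40.5 mL, n = 2 × [61.5 × (1.960 + 0.842) / 40.5]² = 36.2 per group. Then 36.2 × 1.2 = 43.4, rounded up to 44. This check only fixes the number of allocations; the protocol gives no figure for their predictability.

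**Step 1: certain allocations, with every earlier assignment in the block known.** There are 6 equally likely sequences of two active and two placebo. An allocation is certain once one arm's two places are used.

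| Position in block | Probability that it is certain |
|---|---|
| 1 | 0 |
| 2 | 0 |
| 3 | 1/3 (first two alike) |
| 4 | 1 |

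Sum = 4/3 per block. Share = (4/3) / 4 = 1/3, and 88 / 3 = 29.3 women.

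**Step 2: best guess, same condition.** The observer always backs the arm with more places left, and tosses a coin when they are equal. Success by position is 1/2, 2/3, (1/3 × 1 + 2/3 × 1/2) = 2/3, and 1. Sum = 2.833, and 2.833 / 4 = 70.8%, or 62.3 of 88, against 44 by chance.

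**Step 3: partial recognition.** Let each earlier set be recognised independently with probability q. The protocol gives no value, so q is an assumption. Certainty requires both sets of one arm to have been recognised. Position 3 contributes q²/3 and position 4 contributes q². The share is (4/3)q² / 4 = q²/3.

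| q (assumed) | Certain share | Of 88 |
|---|---|---|
| 1.00 | 33.3% | 29.3 |
| 0.75 | 18.8% | 16.5 |
| 0.50 | 8.3% | 7.3 |
| 0.25 | 2.1% | 1.8 |
| 0 | 0% | 0 |

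**Step 4: varying blocks.** Blocks of 4, 6 and 8 in random order were simulated for 88 women. The observer knows every earlier assignment and which sizes are in use, but not where blocks end.

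| Design, full recognition | Certain, of 88 | Best guess correct, of 88 |
|---|---|---|
| Fixed 4 | 29.3 (33%) | 62.3 (71%) |
| Random 4/6/8 | about 2 (2%) | 59.7 (68%) |

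Varying the blocks removes about 27 certain allocations, but only 62.3 − 59.7 = 2.6 correct guesses.

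**Step 5: when block size matters.** There are three cases.

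1. Capsules cannot be told apart: nothing is inferred, and block size is irrelevant.
2. The arm can be felt through the sealed envelope: the next assignment is learned directly, whatever the block size.
3. Opened capsules reveal the arm but sealed envelopes do not: the figures in steps 1 to 4 apply, and the change helps.

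**The case against.** The strongest reply is that the placebo is the whole problem. With a matched capsule, fixed blocks would leak nothing; with a cue that passes through the envelope, varied blocks would protect nothing. This largely stands. The benefit is confined to the third case in step 5, and the protocol does not show which case applies.

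A reader might infer that a third of allocations will be known. The documents do not support that. They state that providers and participants are masked, and nothing in them says that staff can distinguish the capsules. One third is what full recognition would give, not an expected leak.

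A reader might also infer that the blocks bias the day-3 weighing by revealing the arm. A nurse who recognises capsules already knows that woman's arm from the capsules. Changing the blocks would leave this as it is, so it does not count towards this point.

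The protocol also limits selection: consent precedes delivery, enrolment is consecutive, the envelope is taken once a woman qualifies, and the first capsule is due within six hours of birth. These leave little room for delay. They do not remove discretion over exclusions judged after delivery, or over the order of women who qualify at about the same time.

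Finally, fixed blocks of four are an ordinary choice in a masked trial, and the protocol does not contradict itself here. That is fair, and it is why the point is an improvement rather than an error.

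**Conclusion.** The point holds as a minor, low-cost improvement. The block size is fixed and published, the series is single and unstratified, and the placebo is not described as matched on weight. Under full recognition of opened sets, 33% of allocations (29 of 88) could be known in advance. At assumed recognition of 0.75 to 0.25 the share is about 19% to 2%, and with perfect masking it is nil. These figures assume independent recognition of each set, known block boundaries, and sealed envelopes that give nothing away.

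The consequence attributable to the blocks is selective enrolment or ordering. No bias in mL can be derived from the documents. Awareness of the arm at weighing, and any cue from a sealed envelope, belong to the unmatched placebo. That is the root problem, and it would remain after this change.

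**What to change.** In Materials and methods, replace the block-of-four wording with text such as: *The allocation sequence uses randomly permuted blocks of varying size, generated by the co-investigator who has no contact with participants. Block sizes are withheld from the nurses who enrol women or measure outcomes until the database is locked.* Sizes of 4, 6 and 8 in random order would serve; they should stand in the co-investigator's list and not in the published text.

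If recruitment has begun, regenerate only the unused part of the list, starting after a completed block of four so that the part already used is balanced.

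The cost is a new list, relabelling of any unused envelopes already packed, and a possible final imbalance of at most 4 women (half the largest block), with negligible effect on power. The change does not replace action on the placebo capsule, which should come first.
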